## Abstract

**Introduction:**

Each year in the UK, 140 000 patients are discharged from intensive care units (ICUs) to general hospital wards, almost all with complex rehabilitation needs. 84% of patients still require nutritional support and 98% are not physically independent. Despite this, many are discharged from ICU without a nutrition plan, and failure to recognise malnutrition is common. Consequently, malnutrition persists in the ward environment, leading to poor outcomes and acting as a barrier to successful physical rehabilitation. This transition from intensive care to the ward represents a key stage in the recovery journey, and a window for optimising physical independence prior to hospital discharge, decreasing the need for support in the community. However, uncertainty as to how best to provide ongoing rehabilitation which combines adequate nutrition and exercise on the general ward has driven widespread variation in practice.

We have previously shown the benefits of delivering a structured rehabilitation strategy in the ICU. However, the ward environment poses different challenges to the development of an integrated rehabilitation pathway. There is a need to evaluate the clinical and cost-effectiveness of structured rehabilitation strategies when delivered outside the ICU.

**Methods and analysis:**

Physiotherapy and Optimised Enteral Nutrition In the post-acute phase of critical illness is a bi-centre, mixed methods feasibility randomised controlled trial (RCT). 60 patients will be recruited from ICUs at two acute National Health Service Trusts and randomised on a 1:1 basis to receive either individualised physiotherapy and optimised nutrition post discharge from ICU (intervention) or standard care. The primary objective is to assess the acceptability of the intervention and feasibility of a future, multicentre RCT. The primary outcome measures, which will determine feasibility, are recruitment and retention rates, and intervention fidelity. Acceptability of the intervention will be evaluated through semistructured interviews of participants and staff. Secondary outcome measures include collecting baseline, clinical and outcome data to inform the power calculations of a future definitive trial.

**Ethics and dissemination:**

Ethical approval has been obtained through the Wales Research and Ethics Committee 2 (24/WA/0050). We aim to disseminate the findings through international conferences, international peer-reviewed journals and social media.

**Trial registration number:**

NCT06159868. Prospectively registered on 28 November 2023.

STRENGTHS AND LIMITATIONS OF THIS STUDYThis mixed methods study will evaluate the impact of enhanced physiotherapy and optimised nutrition for survivors of critical illness.Qualitative and quantitative approaches will be used to comprehensively assess study outcomes and to inform a main trial and whether or not it would be feasible.The outcomes to be assessed by the study are relevant to patients, clinicians and commissioners.The recruitment and randomisation of study participants from two sites will increase the generalisability of findings.A potential limitation would be the acceptability of the intervention to both patients and staff, which may limit intervention fidelity.

## Introduction

Each year, around 140 000 adults (86% survival rate) are discharged alive from UK intensive care units (ICUs). These individuals frequently have ongoing psychological and physical morbidity, which may persist for many years after discharge.^1^ National guidance developed by the National Institute for Health and Care Excellence and the Intensive Care Society states the need for early and structured rehabilitation for patients admitted to ICU.^2 3^ Despite clear evidence for rehabilitation within the ICU, evidence to support the optimal method for ongoing ward-based rehabilitation is uncertain.

For patients discharged from ICU, suboptimal access to the multidisciplinary team contributes to physical deconditioning and malnutrition. Consequently, on step down to the ward environment, over half of patients experience a deterioration in physical status.^4^ This particularly affects those who leave the ICU most debilitated, with patients who are unable to stand prior to ICU discharge more likely to miss ward-based rehabilitation sessions,^5^ spend longer times in hospital^6^ and are significantly more likely to need ongoing rehabilitation following hospital discharge.^7^ This transition to the ward represents a key stage in the recovery journey, but widespread variation in care across the UK has led to uncertainty as to how best to provide the essential rehabilitation required in the acute setting. High-quality evidence is urgently needed to inform practice and improve outcomes.

The development and widespread implementation of structured, individualised interventions to support patients on ICU step down has the potential to improve overall recovery and quality of life. The James Lind Alliance Intensive Care Priority Setting Partnership highlighted the need for research on supporting recovery after intensive care as a key research priority.^8^

### Rationale for the trial

Patients discharged from intensive care to the ward have complex, multifactorial rehabilitation needs.^9^ To ensure a seamless transition between areas, there is a strong consensus that handover documentation between ICU and wards should be in written form, standardised and structured.^10^,^13^ Despite this, rehabilitation needs are poorly documented in the clinical record, limiting identification and management of ongoing care needs.^10 11 14^ This problem is further compounded due to a lack of cohorting of these patients, who instead are spread throughout the wards in a hospital depending on the original specialty of their underlying admission. This results in widespread variations in care provided, both geographically and in the underlying skills of the receiving wards, meaning post-ICU care commonly misses key patient needs.

Over three-quarters of UK ICUs provide follow-up teams intended to optimise the care of patients in hospital following an ICU stay.^15^ The purpose of follow-up teams is to aid the transition to the ward, support the ward teams with ongoing care such as tracheostomy weaning, improve lines of communication between services and identify clinical deterioration.^2 3^ These teams were often developed with little evidence to support their practice, and the ICU Getting it Right First-Time report and a recent systematic review demonstrated wide variation in provision.^16 17^ The REFLECT study demonstrated follow-up visits failed to ensure key aspects of care were delivered. In addition, follow-up visits usually ceased 24–48 hours after ward transfer despite ongoing clinical problems^18^ limiting the possible impact on post-ICU recovery, and a recent systematic review found no impact on ICU readmission or death.^17^

Two key challenging areas of care provision post-ICU discharge are mobilisation and nutrition. Even in ICUs with established programmes of early mobilisation, around 50% of patients are discharged to the ward unable to stand or transfer to a chair.^19^ Despite these low levels seen at ICU discharge, patient mobility levels actually continue to decrease in the days following step down to the ward.^4 20^ Alongside insufficient handovers of care mentioned above, this is caused by limited provision of rehabilitation in the ward environment, with patients receiving physiotherapy an average of two times per week.^5^ Patients are commonly malnourished at discharge from ICU to the ward.^21 22^ Despite this, many are discharged from ICU without a nutrition plan, and failure to recognise that patients are nutritionally depleted is common.^18^ As a result, inadequate nutrition persists in the ward environment,^23^ with poor outcomes and barriers to rehabilitation directly associated with complex nutritional requirements.^24 25^ The immediate post-ICU discharge phase therefore represents a crucial window, with 98% of patients requiring physiotherapy and 70% being at risk of malnutrition.^9^

In non-ICU populations, increased nutritional support (both protein and energy) has been shown to be cost-effective and associated with improved quality of life and maintenance of functional status.^26^ However, to date, nutrition as an individual intervention, either in the form of protein or energy supplementation, has failed to demonstrate improved outcomes in critically ill patients.^27^ Additionally, exercise alone is catabolic and requires amino acids to stimulate muscle protein synthesis, with energy required for driving such processes and performing exercise.^28^ We hypothesise that a combined approach of structured rehabilitation and optimised nutrition is therefore essential to support recovery in survivors of critical illness.

The Physiotherapy and Optimised Enteral Nutrition In the post-acute phase of critical illness (PHOENIX) mixed methods feasibility randomised controlled trial (RCT) has been designed with the primary aim of assessing the acceptability of the intervention, and recruitment, randomisation and follow-up rates to inform the design of a future adequately powered multicentre trial.

The primary objectives of the feasibility study are

Proportion of patients agreeing to take part out of all those invited (recruitment rate).Proportion of participants who complete the intervention (retention rate).Percentage of intervention sessions completed (intervention fidelity).Intervention acceptability to participants and service providers.

The secondary objectives are

To evaluate a range of clinical and patient-reported outcome measures to aid selection of the most appropriate primary outcome measure for a definitive trial, with estimates for sample size calculation and health economic evaluations of any future definitive trial.

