### Outcome measures

#### Primary outcome measures

Recruitment rate, overall and by centre.Retention rate, defined as the proportion of participants that complete the primary outcome.Intervention adherence measured by the proportion of enhanced physiotherapy sessions completed and nutrition delivery compared with targets.Acceptability of the intervention to participants and service providers.

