### Sample size

Since this is a feasibility study, the sample size is not determined by a power calculation but rather aims to estimate the rate of recruitment and retention to inform the future trial. We aim to recruit a total of 60 patients, with an equal number (maximum of n=30) from each site and equal random allocation to control and intervention groups. The sample size enables a high probability of continuing to a definitive RCT. For example, for retention rate, progression to definitive RCT will be considered if the estimate is ≥40%. The probabilities of getting a retention estimate ≥40% in each group when the true rates are 50% (low rate) and 80% (a good rate in definitive RCTs) are 0.82 and 1, respectively, which are high. We estimate that we will have sufficient data to identify key issues and themes after having interviewed approximately five members of staff and eight patients from each site unless saturation is deemed to be achieved before this point.

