### Data analysis

Results will be reported in accordance with the Consolidated Standards of Reporting Trials extension to randomised pilot and feasibility trials^30^ and the Consolidated Criteria for Reporting Qualitative Research.^31^

For each of recruitment, retention and outcome measure completion data, rate (as a percentage) and corresponding 95% CI will be computed. Outcomes data (including health economic data) will be analysed descriptively by an appropriate member of the research team using means, range and measures of variance (CIs, SD) for continuous variables, and count (n) and percentages (%) for categorical variables. Distribution of DAOH-30 and DAOH-90 data will be explored to determine the best model to use to analyse them (eg, whether t-test or a model for count data) and to plan a definitive RCT.

Intervention fidelity will be assumed if 70% of planned sessions are completed from those available and broken down by facilitator to examine variation between provider sites. During fidelity scoring, examples of good practice will be identified for training during the main trial. A traffic light system shown in table 2 that is recommended for best practice will be used as a guide for progression to a definitive trial.^32^

**Table 2 T2:** ‘Traffic light’ system to determine progression to a definitive trial

	Green(trial feasible)	Amber(may be feasible with modification)	Red(likely unfeasible)
Recruitment of proposed rate (%)	100%(60 participants)	99%(36–59 participants)	<60%(<36 participants)
Retention rates—defined as collection of primary outcome measure (days alive and out of hospital)	100%(60 participants)	60–99%(36–59 participants)	<50%(<36 participants)
Intervention fidelity (physiotherapy)Proportion of available sessions completed	> 70%	40–70%	<40%
Intervention fidelity (nutrition)Proportion of prescribed supplements taken	>70%	40–70%	< 40%

Verbatim anonymised transcripts of semistructured interviews will be thematically analysed.^33^ Codes and themes will be identified from the data and refined using an iterative process. Analysis of interview transcripts will be supported by NVivo V.12 (NVivo qualitative analysis software; QSR International V.12).

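### The recruitment rate is defined as agreed out of invited, but Table 2 bands enrolment against the target of 60, and its amber percentage is wrong as printed

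*Protocol article*

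**What the plan says.** The first primary objective, listed at the end of Rationale for the trial, is "Proportion of patients agreeing to take part out of all those invited (recruitment rate". Its denominator is therefore the number of patients invited. The abstract gives this outcome a deciding role: "The primary outcome measures, which will determine feasibility, are recruitment and retention rates, and intervention fidelity". The section Primary outcome measures lists it again as "Recruitment rate, overall and by centre", without restating the denominator. Data analysis then plans an estimate: "For each of recruitment, retention and outcome measure completion data, rate (as a percentage) and corresponding 95% CI will be computed".

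The progression criteria are in Table 2 of Data analysis, which the text describes as a guide to whether a definitive trial follows. Its single recruitment row is labelled "Recruitment of proposed rate" and has three bands: green at 100% (60 participants), amber at "99%(36–59 participants", and red at "<60%(<36 participants". The figure of 60 is the target in Sample size: "We aim to recruit a total of 60 patients, with an equal number (maximum of n=30) from each site".

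**The concern.** Two different quantities are both called recruitment. One is a consent proportion, with everyone invited as the denominator. The other is enrolment yield, with a target chosen in advance as the denominator. Yield depends on how many patients were eligible and approached as well as on how many agreed. The quantity defined as a primary objective therefore has no place in the progression table, although the abstract says it helps to determine feasibility.

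The distinction matters for planning the definitive trial. Low consent raises questions about the approach to patients and the acceptability of the trial. Too few eligible patients raises questions about the number of sites and the breadth of the eligibility criteria. A head-count alone cannot tell these apart.

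A second, smaller problem is in the same row. The amber percentage does not match its own participant counts.

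**Working it through.** **Inputs**
- Target of 60, at most 30 per site (Sample size).
- Recruitment bands of 60, 36–59 and fewer than 36 participants (Table 2).
- Two sites (Study setting), open from 1 May 2024 to 31 January 2025, which is nine months (General design).
- Logs of all patients approached, kept at each site (Data management).
- Number invited, or expected consent proportion: not given. Any value used below is an assumption.

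**Step 1. Find the denominator in Table 2.** Percentage = participants / denominator. With 60 as the denominator:
- 60/60 = 100%, the printed green value.
- 36/60 = 60%, the printed red boundary; 35/60 = 58.3% falls below it.

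Both printed figures are reproduced, so the row measures enrolled/60 and not agreed/invited.

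**Step 2. Check the amber cell.** 36/60 = 60.0% and 59/60 = 98.3%. The counts 36–59 therefore span 60.0–98.3%, and no count in the band gives 99%. The retention row of the same table prints 60–99% for the same counts, which suggests that the lower limit was lost from the recruitment row.

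**Step 3. Ask whether the planned CI fits either quantity.** A percentage with a 95% CI is natural for agreed/invited, where each invited patient either agrees or does not. It has no ordinary binomial meaning for enrolled/60, because 60 is a chosen target that also caps enrolment (30 per site). The estimate that is planned and the criterion that is applied are therefore not the same quantity.

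**Step 4. Illustrate the consequence.** Assume that everyone who agrees is enrolled, and that approached means invited. Consent proportion = enrolled / invited, with Wilson 95% CI:

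| Enrolled | Invited (assumed) | Consent proportion | 95% CI | Table 2 |
|---|---|---|---|---|
| 60 | 80 | 75% | 64.5–83.2% | green |
| 60 | 300 | 20% | 15.9–24.9% | green |

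The two intervals do not overlap, but the colour is the same. The number of invitations needed to reach 60 is 60 / consent proportion: 600 at 10%, 300 at 20%, 150 at 40%, 120 at 50%, 80 at 75%, and 67 at 90% (rounded up). Every one of these is green if 60 are enrolled.

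**Step 5. See what the head-count does capture.** 60 / (2 sites × 9 months) = 3.3 participants per site per month. With the window and the number of sites fixed, enrolment against 60 is this accrual rate multiplied out.

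**The case against.** The strongest reply is that nothing is lost. The sites log everyone approached, the recruitment percentage will be computed with a 95% CI, and it is to be given overall and by centre. Those who plan the definitive trial will have the consent proportion whether or not it has a coloured cell. Table 2 is only a guide, so a figure such as 60 of 300 can be weighed beside a green row. Acceptability is also a primary outcome without a row in the table, so a missing threshold is not in itself an error. Judging progression on enrolment in a fixed window is a legitimate choice. All of this stands, and it limits the harm.

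It does not remove the mismatch. The objectives and the abstract attach the decision to one quantity, and the table tests another under nearly the same name. A separate analysis plan could add detail but would not reconcile these two statements as published.

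A reader might infer more than the documents support:
- **That the trial will be declared feasible at 20% consent.** The 20% and 75% are illustrations. Reaching 60 at 20% needs 300 invitations, or 300/(2 × 9) = 16.7 per site per month, and nothing shows that so many eligible patients exist.
- **That a red verdict with high consent would be perverse.** Sites that enrol 35 of 60 in the planned window have shown a real feasibility problem, whatever proportion agreed.
- **That accrual is ignored.** Step 5 shows that it is built into the existing row.

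On the amber cell, a typesetting or text-extraction loss cannot be excluded, and the participant counts leave the intended band clear.

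**Conclusion.** The point holds as an inconsistency in the progression criterion. The primary recruitment measure is defined on patients invited, but the recruitment row of Table 2 is enrolment as a percentage of 60, and the consent proportion has no stated part in the progression table. This follows from the printed definition and from the reproduced bands (36/60 = 60%, 60/60 = 100%), and needs no assumption about how many patients will be invited. The size of any effect on the decision cannot be derived, because the article gives neither the number invited nor an expected consent proportion.

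The amber percentage is wrong as printed (99% against 60.0–98.3%). This is minor and does not bear on the main point.

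The documents do not support a claim that consent data are missing or that a wrong decision will follow. Data collection and estimation are unaffected. What needs repair is the naming of the row and a statement of how the consent proportion enters the decision.

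**What to change.** 1. Rename the Table 2 row *Enrolment against target of 60 by 31 January 2025* and keep its participant bands.
2. State that the consent proportion (enrolled/invited, overall and by centre, with 95% CI, from the approach logs) is a separate recruitment measure and is weighed in the progression decision. If cut-offs are attached to it, set and justify them before the logs are analysed.
3. Correct the amber cell to 60–99% (36–59 participants). This follows the convention of the retention row; the exact span is 60.0–98.3%, so the counts should govern.

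The cost is a few lines of text and one table cell. No new data are needed, since the logs already hold the denominator. There are two downsides. The decision gains one more criterion that could prove less favourable. Also, the reported protocol version is dated 3 October 2024, five months after recruitment was due to open, so any cut-offs added now would be set after recruitment has begun, and the report should say so.

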### Intervention

The intervention consists of a combination of structured, individualised physiotherapy and optimised nutrition, beginning immediately following recruitment and continuing for up to 14-days or hospital discharge, whichever is sooner. The physiotherapy or nutritional intervention will be terminated early if no longer deemed to be clinically required or appropriate (eg, patent deterioration and receiving end-of-life care; enteral nutrition becomes contraindicated).

The enhanced physiotherapy intervention will be delivered by a dedicated team led by a physiotherapist. The intervention comprises (1) completion of a comprehensive physical and non-physical assessment to create an individualised treatment plan, (2) setting of patient-centred rehabilitation goals with regular reassessment, (3) provision of daily physiotherapy (Monday–Friday), targeting the highest level of mobility attainable and delivery of individualised exercise programmes and (4) close working with ward staff to optimise treatment delivery and ensure seamless transitions of care once the enhanced intervention is complete.

The nutritional component will be led by a specialist dietitian. A comprehensive nutritional assessment will be completed on day one of the intervention period to include current nutritional intake from oral diet, nutritional supplements and enteral tube feeding. Indirect calorimetry (QNRG+) will be used where possible to determine resting energy expenditure, and protein requirements will be calculated using weight-based equations. An individualised nutritional plan will be devised, to include dietary modification, additional food provision, prescription of oral nutritional supplements or modification to enteral feeding regimen as required. This may also include prescribed nutritional supplementation used within 2 hours of the physiotherapy session to address the catabolic nature of exercise. Review and adjustment to the nutritional care plan will occur daily (Monday–Friday) throughout the intervention period. At the end of the intervention period, patients will be transferred to standard dietetic care, with a comprehensive handover provided.

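### Retention is defined as completing the intervention in the objectives but as outcome collection elsewhere, and Table 2 counts it out of a fixed 60, so a recruitment shortfall is scored again as poor retention

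*Protocol article*

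**What the plan says.** The protocol article describes retention in four places.

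- **Primary objectives** (list at the end of Rationale for the trial): "Proportion of participants who complete the intervention (retention rate".
- **Primary outcome measures**: "Retention rate, defined as the proportion of participants that complete the primary outcome".
- **Data analysis, Table 2** (progression to a definitive trial): "Retention rates—defined as collection of primary outcome measure (days alive and out of hospital". Green is 100% with 60 participants, amber is "60–99%(36–59 participants", and red is fewer than 36 participants. The recruitment row uses the same counts, so 36 to 59 recruited is an allowed amber result.
- **Sample size**: "We aim to recruit a total of 60 patients, with an equal number (maximum of n=30) from each site and equal random allocation". Retention is then evaluated arm by arm, with a stated probability of 0.82 (true rate 50%) and 1 (true rate 80%) of reaching the threshold.

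Two other sections bear on this. Usual care describes routine ward care with no further input from the ICU therapy teams. Secondary outcome measures names DAOH within 30 days as the proposed primary outcome of the definitive trial and assigns 0 to a death in that period.

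**The concern.** Completing a course of treatment and having an outcome recorded are different quantities. The first belongs to adherence, which the protocol already lists as a separate primary outcome. It also cannot be evaluated in the usual-care arm, so the objective as worded cannot be met for half of the planned sample.

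The second fault is in the decision rule. A retention rate should describe what happened to those who entered the trial. A count out of 60 mixes that with how many entered. Because Table 2 already has a recruitment row, a shortfall is penalised there and then again under retention. The progression decision could then suggest a follow-up problem that does not exist.

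**Working it through.** **Inputs.** Target 60, equal allocation, so 30 per arm (Sample size). Table 2 retention counts: 60, 36–59, below 36. Other counts below are assumed for illustration and marked as such.

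**1. The plan's own figure.** With X the number retained in one arm of 30, P(X ≥ r) = Σ C(30,k) p^k (1−p)^(30−k), summed over k = r to 30. The threshold of 40% is 12 of 30.

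- p = 0.5: P(X ≥ 12) = 0.900; P(X ≥ 13) = 0.819; both arms at least 12 = 0.8998² = 0.810.
- p = 0.8: all three are 1.000.
- All 60 taken together, p = 0.5: P(X ≥ 24) = 0.954; P(X ≥ 25) = 0.922.

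The stated 0.82 agrees with P(X ≥ 13), and is close to the both-arms figure. Neither calculation on 60 comes near it. The calculation therefore used 30 per arm, and so assumes that retention can be measured in the usual-care arm.

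**2. The definitions side by side.** Assume 60 randomised, 20 of 30 intervention participants finishing the course, and DAOH collected in 57.

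- Objective's wording: 20/30 = 66.7%, or 20/60 = 33.3% if controls are put in the denominator.
- Outcome section and Table 2: 57/60 = 95.0%.

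This shows only that the wordings measure different things.

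**3. The denominator in Table 2.** 60/60 = 100% and 36/60 = 60%, which matches the printed pairs, so the counts assume that 60 were randomised. Let N be the number randomised and c the number with DAOH (both assumed):

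| N | c | c/N | By percentage | c/60 | By count |
|---|---|---|---|---|---|
| 60 | 54 | 90.0% | amber | 90.0% | amber |
| 50 | 50 | 100% | green | 83.3% | amber |
| 45 | 43 | 95.6% | amber | 71.7% | amber |
| 40 | 35 | 87.5% | amber | 58.3% | red |
| 36 | 36 | 100% | green | 60.0% | amber |

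**4. The general rule.** The count is red when c < 36, which on the scale of those randomised is c/N < 36/N: 60% at N = 60, 72% at N = 50, 80% at N = 45, 90% at N = 40 and 100% at N = 36. At N = 36, still amber for recruitment, one missing DAOH gives 35/36 = 97.2% and a red count. Green by count is impossible for any N below 60.

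**The case against.** The best defence is that the operative definition can be recovered. The outcome section and Table 2 both say explicitly what retention is, and they agree. The primary aim in the Rationale speaks of follow-up rates, which fits them. The objective is one line in a list. This stands: the objective is the outlier, and it would be wrong to say that retention has no usable definition. Table 2 is also described as a guide, so nobody is bound to follow a misleading count.

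A reader might infer more than the document supports:

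- *The same data are green under one definition and amber under the other.* Table 2 attaches its colours to a row "defined as collection of primary outcome measure (days alive and out of hospital". No traffic light is applied to completing the intervention under the name of retention, so the 66.7% above has no colour.
- *Stopping treatment early counts as non-retention.* The Intervention section says treatment "will be terminated early if no longer deemed to be clinically required or appropriate", but nowhere says that this is non-completion.
- *DAOH will be near-complete from records even if few attend follow-up.* This is conjecture. Data management describes chart extraction up to hospital discharge and no further collection after withdrawal, and DAOH counts only time at home or usual residence.
- *Recruiting 35 and following all 35 shows the fault.* It adds little, because recruitment is already red at that number.
- *Feasibility of follow-up goes unassessed.* Data analysis already plans completion rates with 95% CIs for the outcome measures. A further progression criterion would be a preference, not a correction.

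None of this answers the denominator fault, which lies within the operative definition.

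**Conclusion.** The point holds as an internal inconsistency with two parts. The objective's wording conflicts with the outcome section and Table 2 and cannot apply to usual care. The fixed counts in Table 2 misstate retention whenever fewer than 60 are randomised, a result the table itself foresees.

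The size depends on the shortfall. There is no effect at 60. At 50 with complete data, green becomes amber. At 40 with 35 collected, retention of 87.5% becomes red. The numbers randomised and collected are illustrative. The colours by count assume that the count is followed where it disagrees with the percentage; the table does not say which governs.

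Two neighbouring inconsistencies are separate and add no weight here. The red retention cell pairs below 50% with fewer than 36 participants, although 36/60 is 60%. The Sample size section says that "progression to definitive RCT will be considered if the estimate is ≥40"%, a level that Table 2 would class as red.

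**What to change.** 1. Define retention once, in the objectives, the outcome section and Table 2: participants with DAOH-30 determined, divided by all randomised, overall and by arm. State that a death within 30 days counts as determined, with value 0.
2. In the Table 2 retention row, replace the counts out of 60 with percentages of those randomised. The range from 50% to just under 60% then has to be assigned to a colour, because the present red percentage and red count disagree.
3. Report completion of the intervention under adherence, for the intervention arm only.
4. Report the outcome-completion rates and 95% CIs already planned in Data analysis alongside. No new progression criterion is needed.

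The cost is one line in the objectives, matching wording in the outcome section and one table row. No additional data, visits or participants are required. The change should be made before the progression criteria are applied to the results.
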